##### Premedications

All neonates of both groups will receive pre-procedural medications, according to local protocols. Suggested schemes are as follows:

- Intravenous atropine (10 µg/kg) in 1 min followed by intravenous fentanyl: 0.5 µg/kg by pump infusion in no less than 5 min (possibly repeatable dose if satisfactory analgosedation is not obtained)

or

- Intravenous atropine (10 µg/kg) in 1 min followed by intravenous ketamine: 0.5 mg/kg in no less than 1 min (possibly repeatable dose if satisfactory analgosedation is not obtained)

The method of premedication will be documented in each participating center.

##### IN-REC-SUR-E group

Infants randomly assigned to the IN-REC-SUR-E group will receive pre-intubation medications and will start after intubation on high-frequency oscillatory ventilation (HFOV) using the following ventilator settings: mean airway pressure 8 cmH_2_O, frequency 15 Hz, and volume guarantee 1.5–1.7 mL/kg [17]. The inspiratory to expiratory ratio will be 1:1. Infants will undergo an oxygenation-guided lung recruitment procedure using stepwise increments and then decrements in the mean airway pressure to recruit and stabilize collapsed alveoli using the de Jaegere method [18]. In particular, optimal recruitment is defined as adequate oxygenation using a FiO_2_ of 0.25 or less. Starting at 8 cmH_2_O, the mean airway pressure will be increased stepwise (2 cmH_2_O every 2–3 min) as long as SpO_2_ improves. The FiO_2_ will be reduced stepwise, keeping SpO_2_ within the target range (90–94%). The recruitment procedure will be stopped if oxygenation no longer improves or if the FiO_2_ is equal to or less than 0.25. The corresponding mean airway pressure will be called the opening pressure. Next, the mean airway pressure will be reduced stepwise (1–2 cmH_2_O every 2–3 min) until the SpO_2_ deteriorates (of at least 2–3 percentage points). The corresponding mean airway pressure will be called the closing pressure. After a second recruitment maneuver at the opening pressure for 2 min, the optimal mean airway pressure will be set at 2 cmH_2_O above the closing pressure for at least 3 min. Immediately after the recruitment procedure, infants in the IN-REC-SUR-E group will receive 200 mg/kg of poractant alfa (Chiesi Farmaceutici S.p.A., Parma, Italy) via a closed administration system in one or two aliquots, while continuing high-frequency oscillatory ventilation. Infants with sufficient respiratory drive and stable clinical conditions will be extubated within 30 min after surfactant administration irrespective of the FiO_2_ and will recommence on nasal CPAP (7–9 cm H_2_O) [19] or NIPPV. Cases of failure to extubate due to complications or intercurrent conditions will be reported, defined, and included in the statistical analysis.

##### LISA group

By contrast, infants allocated to the LISA group will receive 200 mg/kg of poractant alfa (Chiesi Farmaceutici S.p.A., Parma, Italy) according to the following protocol: during nasal CPAP with a pressure of 7–8 cm H_2_O, surfactant will be administered over 0.5–3 min using the SurfCath™ tracheal instillation catheter (VYGON S.A. – Ecouen, France), or a 4–6-F end-hole catheter, according to local protocols. After pre-procedural medications, the catheters will be positioned during laryngoscopy with or without Magill forceps. The catheter will be connected to a syringe pre-filled with the surfactant, and the surfactant is instilled slowly. The infant’s mouth will be closed. In cases of apnea or bradycardia, positive pressure ventilation will be performed until recovery by nasal prongs or mask or by endotracheal tube if necessary. After surfactant administration, CPAP (7–9 cm H_2_O) [19] or NIPPV will be provided unless failure criteria are met (see below).

Transcutaneous PaCO_2_ will be recorded during surfactant administration in both procedures (IN-REC-SUR-E and LISA), if available. Changes in respiratory support settings are permitted to maintain transcutaneous CO_2_ values in each site’s accepted range.

In both groups, maintaining a FiO_2_ < 0.30 to obtain SpO_2_ values in the desired range (90–94%) will drive weaning of the level of CPAP or in the rate of NIPPV in the following days. In the babies managed with CPAP, the decision as to whether to begin bilevel-positive airway pressure or NIPPV to prevent the need for re-intubation in infants of both groups will be up to the neonatologist on duty and will be considered in the final analysis.

Infants in both groups who meet the CPAP/NIPPV failure criteria again during the following 24 h will receive a second dose of surfactant (100 mg/kg of poractant alfa) according to the randomized group (IN-REC-SUR-E or LISA). The minimum time interval between the first and second doses of surfactant is 6 h. In case of respiratory deterioration requiring endotracheal intubation immediately after the first surfactant administration, this will be interpreted as extubation failure in the INRECSURE group or as severe respiratory failure requiring intubation in the LISA group.

The indications for invasive mechanical ventilation via endotracheal tube after IN-REC-SUR-E or LISA will be as follows:

Poor oxygenation with FiO_2_ above 0.40 for more than 6 h to maintain a SpO_2_ between 90 and 94% despite CPAP (7–9 cm H_2_O) or NIPPV (with peak inspiratory pressure of 15–20 cmH_2_O, positive end-expiratory pressure of 6–8 cmH_2_O, and rate of 40–60 breaths/min)Respiratory acidosis (either capillary pCO_2_ or PaCO_2_ > 65 mm Hg [8.5 kPa] and pH < 7.20)Apnea (more than four episodes of apnea per hour or more than two episodes of apnea per hour requiring ventilation with bag and mask), despite optimal nasal CPAP, nasal intermittent positive pressure ventilation, or bilevel positive airway pressure

#### Criteria for discontinuing or modifying allocated interventions {11b}

On the consent form, participants are informed that they can withdraw from the study at any time without losing any rights to treatment, either current or future. Clinical data will be destroyed only if the right to be forgotten will be requested according to GDPR [ref: https://gdpr-info.eu/art-17-gdpr/]. In this case, the record ID and the allocation arm will be traced, and the reason for withdrawal will be recorded in the eCRF. The trial may be stopped if during the trial or after interim analysis, unwanted effects have occurred, new information becomes available and the experimentation is no longer in the best interests of this population, the agreed rules for participation in the trial are not followed, and the trial is interrupted by the component authorities or by the promoter.

#### Strategies to improve adherence to interventions {11c}

Given the nature of the intervention only after adherence to the protocol by the participating centers, no specific strategy is envisaged to improve intervention adherence.

#### Relevant concomitant care permitted or prohibited during the trial {11d}

For ethical reasons, all types of care as usual are permitted during the trial.

#### Provisions for post-trial care {30}

There will not be a specific post-trial care. No harm from participation in the trial is expected. All preterm infants enrolled in the trial, after discharge, will start a “preterm-follow-up program” as a normal clinical practice for all preterm discharged from hospitals participating in the study. Infants enrolled in trials will be tested for neurodevelopmental outcomes and respiratory function at 24 months, the last of the secondary outcomes (see section below).

### Outcomes {12}

#### Primary outcome measure

A composite outcome of death or bronchopulmonary dysplasia (BPD) at 36 weeks’ postmenstrual age [20] is the primary outcome because BPD represents the most severe respiratory morbidity of preterm infants, and death is a competing risk. The diagnosis of BPD will be ascertained by a standardized test [21]. Infants remaining on mechanical ventilation or CPAP at 36 weeks’ postmenstrual age, or those with a supplemental oxygen concentration ≥ 0.30 to obtain SpO_2_ between 90 and 94% will receive a BPD diagnosis without additional testing. Infants with a supplemental oxygen concentration < 0.30 to obtain SpO_2_ between 90 and 94% or those receiving high-flow nasal cannula therapy will undergo a timed stepwise reduction to room air without any flow. Those in whom the reduction will not be tolerated will receive a BPD diagnosis.

#### Secondary outcome measures

The following are the secondary outcome measures:BPD at 36 weeks’ postmenstrual age.Grade of BPD at 36 weeks’ postmenstrual age.Death at 36 weeks’ postmenstrual age or before discharge.SpO_2_/FiO_2_ at 3 days, 7 days, and thereafter every 7 days until 36 weeks’ postmenstrual age [22]Severe intraventricular hemorrhage (IVH) (grade 3 or 4 based on the Papile criteria) [23].Occurrence of air leaks including pneumothorax or pulmonary interstitial emphysema before discharge.Need and duration of invasive respiratory support.Duration of non-invasive respiratory support.Duration of oxygen therapy. Pulmonary hemorrhage. PDAhs (patent ductus arteriosus; hemodynamically significant), i.e., requiring pharmacological treatment with ibuprofen/indomethacin/acetaminophen). Percentage of infants receiving two or more doses of surfactant. Incidence of PVL (periventricular leukomalacia) [24]. Incidence of ROP (retinopathy of prematurity) grade 3 or above [25]. Incidence of NEC (necrotizing enterocolitis) grade 2 or above [26]. Incidence of sepsis defined as a positive blood culture or suggestive clinical and laboratory findings leading to treatment with antibiotics for at least 7 days despite the absence of a positive blood culture. Total in-hospital stay. Use of systemic postnatal steroids. Neurodevelopmental outcomes via Bayley scales of infant development-III and respiratory function testing at 24 months of age. In particular, lung function tests will be performed at 2 years of life according to current American Thoracic Society (ATS)/European Respiratory Society (ERS) guidelines. Tidal breathing flow volume loop (TBFVL) and multiple-breath nitrogen washout (MBNW) will be performed during spontaneous sleep. An appropriately sized face mask will be gently placed covering the mouth and nose of infants lying supine. The reported MBNW outcomes will be the functional residual capacity (FRC) and the lung clearance index (LCI), which represents a measure of the number of times the volume of gas in the lung at the start of the washout (the FRC) must be turned over in order to wash out the tracer to the pre-defined endpoint. Pulmonary function testing will be offered to all infants in selected centers distributed in different geographic areas, equipped with specific devices and with expertise in data interpretation.

### Other collected data

The following data will be recorded for each infant: gestational age (GA), birth weight (BW), BW *z* score, sex, Apgar score at 5 min, antenatal steroid treatment (complete course), preterm PROM > 18 h, diagnosis of clinical chorioamnionitis (defined as maternal fever, uterine tenderness, abdominal pain, foul-smelling vaginal discharge, maternal and fetal tachycardia, elevated white blood cell count), maternal hypertension disorders, and type of delivery.

### Participant timeline {13}

All participants will complete the same outcome assessments as presented in Fig. 1 and Table 1.

**Table 1 Tab1:** Overview of enrolment, interventions, and assessments

	Study period					
	Enrollment	Allocation	Post-allocation			Close-out
Time point	* − t*_*1*_	0	*t*_*1*_	*t*_*2*_***	*t*_*3*_	*t*_*4*_
Enrollment						
Eligibility screen	X					
Informed consent	X					
Allocation		X				
Interventions						
*INRECSURE group*			X	X	X	X
*LISA group*			X	X	X	X
Assessments						
*Information on background and randomization*	X					
*Primary outcome*					X	
*Secondary outcomes*			X	X	X	X
*Other collected data*	X					

− *t*_*1*_ before or after birth, *0* at the time of allocation, *t*_*1*_ first surfactant administration within 2 h of life, *t*_*2*_*** possible second dose of surfactant during the following 24 h after the first dose, *t*_*3*_ at discharge or death, *t*_*4*_ follow up at 24 months of age

### Sample size {14}

In order to assess the superiority of the IN-REC-SUR-E with respect to the LISA technique, we hypothesized that employing the IN-REC-SUR-E technique for surfactant administration in extremely preterm infants could lead to an increased survival rate without BPD at 36 weeks of postmenstrual age compared to the LISA approach, raising it from 65 to 80%. Our estimation of a 15% difference is grounded in data from the German Neonatal Network (GNN) regarding the LISA approach, findings from the recently published OPTIMIST trial [27], and updated information on the IN-REC-SUR-E technique from select Italian centers, which continued its use post the conclusion of the INRECSURE study. To achieve 90% statistical power at a 0.05 significance level, we determined that 181 newborns must be enrolled in each group. Factoring in a 5% risk of including patients who do not meet the inclusion criteria after randomization, a total of 382 patients will be randomly assigned. Twins will be randomized separately.

### Recruitment {15}

The obstetricians are aware of the study protocol and will inform the neonatologists of any case of high-risk preterm birth. Written and oral information will, whenever possible, be offered to parents prior to birth if the mother is at risk for preterm delivery and the infant is likely to be eligible. In the few cases of spontaneous preterm labor and consequent vaginal delivery, the informed consent will be obtained soon after the birth.

A monthly accrual report about the study will be sent to participating centers.

### Assignment of interventions: allocation

#### Sequence generation {16a}

Infants will be allocated to one of the two treatment groups (1:1) according to a restricted randomization procedure [14]. A biostatistician (TP) will generate the allocation sequences using both stratification and permuted blocks with random block sizes and block order. Stratification factors will include center and gestational age (24^+0^ to 25^+6^ weeks or 26^+0^ to 27^+6^ weeks).

#### Concealment mechanism {16b}

The table of allocation will not be disclosed to ensure concealment, and the randomization will be provided through the Research Electronic Data Capture (REDCap) web application (https://redcap-irccs.policlinicogemelli.it/). The assignment to intervention will be unmasked to all trial participants: parents, research staff, and medical team will be only aware of the study group assignment after randomization procedures.

#### Implementation {16c}

Enrollment and assigning participants to interventions will be performed as previously described.

### Assignment of interventions: blinding

#### Who will be blinded {17a}

Except for the biostatistician involved in the analysis, the assignment to intervention will be unmasked to all trial participants: parents, local site research staff, and medical team will be only aware of the study group assignment after randomization procedures.

#### Procedure for unblinding if needed {17b}

Refer to above {17a}.

##### Data collection and management

#### Plans for assessment and collection of outcomes {18a}

Local principal investigators are required to participate in preparatory meetings in which details of the study protocol, data collection, and IN-REC-SUR-E and LISA procedures will be accurately discussed. All centers will receive detailed written instructions on web-based data recording, and, to resolve any difficulties, it will be possible to contact the Research Core Facility Data Collection (Fondazione Policlinico Universitario A. Gemelli IRCCS, Università Cattolica del Sacro Cuore). Moreover, it will be ascertained that IN-REC-SUR-E and LISA procedures are followed similarly in all participating centers.

#### Plans to promote participant retention and complete follow-up {18b}

Each participating investigator will be responsible for ensuring data quality. Each reported information will be systematically checked for consistency, completeness, data processing, and monitoring. All study data will be (1) screened for out-of-range data, with cross-checks for conflicting data within and between data collection forms by a data manager, and (2) referred back to the relevant center for clarification in the event of missing items or uncertainty.

The data manager will keep a record of all discrepancies and resolutions. The chief investigator and trial statistician will review the results generated for logic and for patterns or problems. Outlier data will be investigated.

A monthly accrual report about the study will be sent to participating centers.

#### Data management {19}

A customized electronic case report form (eCRF) will be created for the study. Data processing will take place in compliance with current Italian and European legislation regarding the General Data Protection Regulation. Data sharing with non-European Union centers will be performed according to Standard Contract Clauses. Each participating center will be identified by a three-digit code, and within each center, patients will be identified with a progressive number. Pseudo-anonymized study data will be collected and managed using REDCap electronic data capture tools hosted at Fondazione Policlinico Universitario A. Gemelli, IRCCS (https://redcap-irccs.policlinicogemelli.it/). REDCap is a secure, web-based application designed to support data capture for research studies, providing (1) an intuitive interface for validated data entry, (2) audit trails for tracking data manipulation and export procedures, (3) automated export procedures for seamless data downloads to common statistical packages, and (4) procedures for importing data from external sources [28, 29]. To prevent possible data entry mistakes and to improve data quality, the eCRF will be implemented by design according to validation, branching, and skipping logic quality criteria.

#### Confidentiality {27}

Only people officially registered as study investigators or data managers will receive a user login to access the REDCap web platform and enter/manage data. All collected data will be obtained from the clinical records. Each participating center must maintain appropriate medical and research records for this trial and regulatory/institutional requirements for the protection of the confidentiality of study subjects. The principal investigator is responsible for assuring that the data collected are complete, accurate, and recorded in a timely manner. Clinical information will be collected at the following times:At trial entry: information on eligibility, background information, and randomizationFollowing randomization: all data above listed in the “Primary outcome measure”, “Secondary outcome measure”, and “Other collected data” sections.

Further information will be collected on expected serious adverse events.

#### Plans for collection, laboratory evaluation, and storage of biological specimens for genetic or molecular analysis in this trial/future use {33}

This trial does not involve collecting biological specimens for storage.

## Statistical methods

### Statistical methods for primary and secondary outcomes {20a}

Analyses will adhere to both the intention-to-treat and per-protocol principles, following the recommendations outlined in the CONSORT guidelines, with the primary outcome evaluated in the intention-to-treat population [30]. The intention-to-treat group will encompass all participants assigned to the study intervention, while the per-protocol population will comprise individuals who receive and complete the study intervention, meeting all the study criteria.

For the primary outcome, a log-binomial regression model will be employed, adjusting for the stratification factors of gestational age and study center to estimate the adjusted relative risk (RR). Additionally, we will calculate the absolute risk reduction and the number-needed-to-treat. Statistical analyses will be conducted using the Stata software, version 16.

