**Methods:**

In this study, 382 infants born at 24^+0^–27^+6^ weeks’ gestation, not intubated in the delivery room and failing nasal continuous positive airway pressure (nCPAP) or nasal intermittent positive pressure ventilation (NIPPV) during the first 24 h of life, will be randomized 1:1 to receive IN-REC-SUR-E or LISA surfactant administration. The primary outcome is a composite outcome of death or BPD at 36 weeks’ postmenstrual age. The secondary outcomes are BPD at 36 weeks’ postmenstrual age; death; pulse oximetry/fraction of inspired oxygen; severe intraventricular hemorrhage; pneumothorax; duration of respiratory support and oxygen therapy; pulmonary hemorrhage; patent ductus arteriosus undergoing treatment; percentage of infants receiving more doses of surfactant; periventricular leukomalacia, severe retinopathy of prematurity, necrotizing enterocolitis, sepsis; total in-hospital stay; systemic postnatal steroids; neurodevelopmental outcomes; and respiratory function testing at 24 months of age. Randomization will be centrally provided using both stratification and permuted blocks with random block sizes and block order. Stratification factors will include center and gestational age (24^+0^ to 25^+6^ weeks or 26^+0^ to 27^+6^ weeks).

Analyses will be conducted in both intention-to-treat and per-protocol populations, utilizing a log-binomial regression model that corrects for stratification factors to estimate the adjusted relative risk (RR).

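### If centre enters as one indicator per centre, the log-binomial primary model is likely to have its maximum on the boundary at 382 infants once there are about 15–20 centres

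*Protocol article*

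**What the plan says.** The section on statistical methods {20a} fixes the primary analysis: "a log-binomial regression model will be employed, adjusting for the stratification factors of gestational age and study center", to give an adjusted relative risk. The abstract repeats this. Section {20a} also promises an absolute risk reduction and a number needed to treat, without saying which model they come from. Section {16a} confirms the factors: "Stratification factors will include center and gestational age", the latter in two bands.

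The modelled event is "A composite outcome of death or bronchopulmonary dysplasia (BPD) at 36 weeks’ postmenstrual age". The sample size section {14} expects BPD-free survival to improve "compared to the LISA approach, raising it from 65 to 80" per cent, with 181 infants per arm and 382 in total. It adds: "Twins will be randomized separately".

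The text does not say whether centre enters as fixed indicators, as a random effect or after pooling. It does not give the number of centres, and it names no alternative if the model cannot be fitted.

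**The concern.** A log-binomial model is a binary regression with a log link, so every fitted risk must stay at or below 1. With few covariates and moderate risks this rarely matters. With one parameter per centre, a small centre with many events can push its highest-risk group (LISA arm, lower gestational-age band) up to 1. The maximum then lies on the edge of the permitted region, the score is not zero there, and the usual standard error and Wald interval have no justification. Software may stop without converging, or report figures that cannot be trusted.

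At stake is the primary result. Unless a replacement is fixed beforehand, it would be chosen after the data are in. Blinding the analysing biostatistician ({17a}) reduces that difficulty but does not remove it.

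**Working it through.** **1. The plan's own figures.** Event risks are 1 − 0.65 = 0.35 (LISA) and 1 − 0.80 = 0.20 (IN-REC-SUR-E), so RR = 0.20/0.35 = 0.571. Taking a two-sided test (the sidedness is not stated) and the unpooled formula:

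n = (1.960 + 1.282)² × (0.65×0.35 + 0.80×0.20)/0.15² = 180.96, so 181 per arm.

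362/0.95 = 381.05, so 382. Both figures reproduce, and the point below does not alter them.

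**2. Events available.** The average risk is (0.35 + 0.20)/2 = 0.275, and 0.275 × 382 ≈ 105 events.

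| Centres (assumed) | Infants per centre | Events per centre | Infants per centre × age band × arm |
|---|---|---|---|
| 5 | 76.4 | 21.0 | 19.1 |
| 10 | 38.2 | 10.5 | 9.6 |
| 20 | 19.1 | 5.3 | 4.8 |
| 30 | 12.7 | 3.5 | 3.2 |
| 40 | 9.6 | 2.6 | 2.4 |

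**3. How the boundary is reached.** The protocol gives no risk by age band. Assume 50% and 25% in the LISA arm, with 40% of infants in the lower band: 0.4×0.50 + 0.6×0.25 = 0.35, which agrees with the plan. A centre whose estimated risk is twice the average then has a fitted risk of 0.50 × 2 = 1 in the LISA, lower-band group. With three to five expected events per centre, chance alone can produce such an estimate.

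**4. Simulation.** Each scenario used 200 trials of 382 infants, with RR 0.571, permuted blocks within centre × age band and one indicator per centre. Zero-event centres were set aside, since their coefficient runs to minus infinity. The share of trials with the maximum on the boundary was:

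| Centres | Equal sizes, equal risk | Equal sizes, SD of log risk 0.3 | Uneven sizes, SD 0.3 |
|---|---|---|---|
| 5 | 0% | 5% | 13.5% |
| 10 | 3% | 22.5% | 42% |
| 20 | 34.5% | 66.5% | 80% |
| 30 | 67% | 87.5% | 97.5% |
| 40 | 89.5% | 98% | 99.5% |

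Further runs under similar assumptions gave 2–24% at 8 centres, 11–56% at 12, 14–69% at 15 and up to 85% at 20. The Monte Carlo error of a proportion near 50% is about 1.96 × √(0.25/200) = 7 percentage points, small against these ranges. Plain Fisher scoring without safeguards failed in 57–90% of trials at 20 centres.

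**5. Source of the problem.** A log-binomial model with treatment and age band only had no boundary solutions. The centre terms cause them.

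**6. The alternative.** Modified Poisson with robust variance and the same covariates (zero-event centres again set aside) converged in every trial. Coverage of the 95% interval was 92–97.5%. With 200 trials, 95% ± 1.96 × √(0.95×0.05/200) is 92–98%, so this is compatible with nominal. Its log RR differed from the constrained log-binomial estimate by a median of about 0.02–0.05. With small centres pooled and the variance clustered on the mother, it rejected in 3.7–4.3% of null trials (600 each at 20 and 30 centres).

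**The case against.** The strongest reply is that the text fixes neither of the two facts on which the size depends. Indicators for every centre are a reading, though the ordinary one. The number of centres is unknown, and across all assumptions the failure rate runs from 0% to 99.5%. This stands: a reader might infer that the model will fail, and the document does not support that. It would be a minor risk with 5–8 centres. A larger number is plausible but unproven: 382 infants in 3 years is about 127 a year, so ten centres would each need about 13 eligible, consented infants every year.

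A second reply is that the coding of centre and a fallback belong in the analysis plan or full protocol, which are not shown. This stands in part. Their absence from an article is no fault, and they may exist. But the article commits the primary analysis to a particular model, and a later document that avoids the boundary would have to alter that commitment.

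Two stronger readings should be set aside. A reader might infer that centres with no events also push the fit to the boundary. They do not: their fitted risk goes to 0, they drop out of the likelihood, the treatment RR stays estimable, and Poisson with centre indicators behaves the same way. A reader might also infer that ignoring twin pairs invalidates the test. With individual randomisation in permuted blocks, 10–30% of infants in pairs and within-pair correlation of 0.2–0.5, the ratio of true to naive variance was 0.96–1.02 and the type I error 4.4–5.5%. That is negligible.

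**Conclusion.** The point holds conditionally. With one indicator per centre at 382 infants and about 105 events, the log-binomial maximum often lies on the boundary: about 0–25% of trials with 5–8 centres, 3–42% with 10, 35–85% with 20 and 67–98% with 30. The problem is likely from about 15–20 centres, or from about 10 if sizes are uneven and risk varies.

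This rests on assumed centre numbers and sizes, assumed between-centre variation and an assumed split of risk by gestational age. The effect measure and the choice of adjustment factors are sound, and the sample size is unaffected. The change should be made before the data are seen. It does not call the design into question.

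**What to change.** In {20a}, estimate the adjusted RR by modified Poisson regression (log link, robust variance) with treatment, gestational-age stratum and centre. State a rule, set before the data are seen, for pooling small centres. If the sponsor prefers to keep log-binomial as the primary model, say how centre enters and name the modified Poisson model as the fixed fallback when the fit does not converge or ends on the boundary. Derive the absolute risk reduction and number needed to treat by standardisation from the same fit: average the predicted risks over all infants under each arm and take the difference.

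The cost is a few lines of text and of Stata code. Modified Poisson is slightly less efficient than log-binomial when the latter converges. Individual fitted values can exceed 1, but its estimating equations still match fitted to observed event totals in each arm.

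Clustering the robust variance on the mother is an optional refinement. It needs an identifier linking siblings and has almost no effect on the error rate.

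### The primary model is valid but leaves some precision unused: it adjusts only for centre and a two-band gestational age, although finer baseline data are recorded for every infant

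*Protocol article*

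**What the plan says.** The primary outcome is binary: "A composite outcome of death or bronchopulmonary dysplasia (BPD) at 36 weeks’ postmenstrual age". For its analysis, Statistical methods {20a} specifies a log-binomial regression model, "adjusting for the stratification factors of gestational age and study center to estimate the adjusted relative risk (RR"). The absolute risk reduction and number needed to treat are to be calculated as well, but the section does not say from which model.

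Sequence generation {16a} defines the factors: "Stratification factors will include center and gestational age (24^+0^ to 25^+6^ weeks or 26^+0^ to 27^+6^ weeks"). Gestational age as a stratification factor is therefore a single two-level term.

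The section on other collected data reads "The following data will be recorded for each infant: gestational age (GA), birth weight (BW), BW *z* score, sex", and the same list goes on with "sex, Apgar score at 5 min, antenatal steroid treatment (complete course"). Table 1 places "Other collected data" at enrollment.

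No other section brings these variables into the primary model. Section {20b} uses gestational age for subgroup analysis only, which adds no precision to the overall comparison. Section {20c} rules out imputation of missing data.

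**The concern.** With a two-level term, an infant of 24+0 weeks is given the same baseline risk as one of 25+6, and an infant of 26+0 the same as one of 27+6. Any prognostic information within the bands, and any carried by sex, growth or antenatal steroids, stays in the residual variation. These variables are fixed by birth, so treatment cannot affect them and adjusting for them is safe. If they predict death or BPD, leaving them out makes the interval for the RR wider than the collected data allow, and chance imbalance between arms in these variables goes uncorrected.

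The protocol states this adjustment set as its choice for the primary analysis. It is not a detail left open for the statistical analysis plan. An analysis plan that added covariates would depart from the published protocol.

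**Working it through.** **1. The plan's own sample size.** Inputs from Sample size {14}: survival without BPD 65% v 80%, power 90%, alpha 0.05 (sidedness not stated; two-sided assumed), 5% inflation.

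- Unpooled formula: n = [0.65×0.35 + 0.80×0.20] × (1.960 + 1.282)² / 0.15² = 0.3875 × 10.51 / 0.0225 ≈ 181 per arm. This matches the plan.
- Total: 362 / 0.95 = 381.05, rounded up to 382. This matches too.
- The pooled formula gives 185 per arm, and 89.5% power at 181.

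The sample size takes no credit for covariate adjustment.

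**2. What two bands keep of gestational age.** The age distribution is assumed.

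- Evenly spread over 24 to 28 weeks: total variance 4²/12 = 1.333; within-band variance 2²/12 = 0.333; between-band share (1.333 − 0.333)/1.333 = 75%.
- Density rising linearly towards 28 weeks: total variance 8/9 = 0.889; a quarter of infants fall in the lower band; the band means are 4/3 and 28/9 weeks above 24; between-band variance ¼ × ¾ × (16/9)² = 0.593; share 0.593/0.889 = 67%.

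**3. Gain by approximation.** Let R² be the share of outcome variance that the added covariates explain beyond the strata. The documents do not give it; 0.01 to 0.10 is assumed. Effective n per arm = 181/(1 − R²), and the interval width is multiplied by √(1 − R²). Power uses the pooled formula, 89.5% at R² = 0.

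| R² | Effective n per arm | Power | Interval narrower by |
|---|---|---|---|
| 0.01 | 183 | 89.8% | 0.5% |
| 0.02 | 185 | 90.1% | 1% |
| 0.05 | 191 | 91.0% | 2.5% |
| 0.10 | 201 | 92.4% | 5% |

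**4. Check by simulation.** 2,000 trials of 362 infants were run per scenario, with risk of death or BPD 35% v 20% and a standardised logistic estimate of the risk difference. Assumed log odds ratios per week of gestation, for sex, per SD of birth-weight z score and for steroids (absolute values): weak 0.2 each; moderate 0.45, 0.4, 0.35, 0.4; strong 0.7, 0.6, 0.5, 0.6. Adjustment for the two bands was compared with adjustment for continuous gestational age, sex, z score and steroids.

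| Scenario | Variance ratio | Power, two bands | Power, full |
|---|---|---|---|
| Weak | 0.995 | 89.6% | 89.4% |
| Moderate | 0.980 | 90.6% | 91.7% |
| Strong | 0.917 | 90.4% | 92.5% |

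The Monte Carlo standard error of each power figure is about √(0.9×0.1/2000) = 0.7 points, so the weak scenario shows no detectable change.

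**5. Large-sample calculation for log RR.** Assumed odds ratios: 0.75 to 0.50 per week, 1.2 to 1.7 for sex, 0.8 to 0.55 per SD of z score, 0.8 to 0.6 for steroids. The variance ratio against the two bands runs from 0.987 to 0.933, a reduction of 1.3% to 6.7%. At 382 infants that is worth 382 × (1/0.987 − 1) ≈ 5 to 382 × (1/0.933 − 1) ≈ 27 infants. Power rises from 89.5 to 89.9% (weak) and from 90.6 to 92.4% (strong).

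**6. Can the covariates simply be added to the log-binomial model?** In 300 illustrative trials each, with a basic fitting routine, 49% (moderate) and 89% (strong) of fits failed to converge or gave fitted risks of 1 or more. The estimation method has to change along with the covariate list.

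Centre was left out of every calculation in steps 3 to 6.

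**The case against.** The strongest reply is that nothing here is wrong. Adjusting for the stratification factors matches the randomisation, gives a valid test, and the sample size does not rely on more. That stands.

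The gain is also small and rests on assumptions. The subgroup section supports gestational age as influencing outcomes. The introduction ties low birth weight and low gestational age to IN-SUR-E failure, not to death or BPD. Nothing in the document links sex or antenatal steroids to the primary outcome. That stands too, and it is why the gain is given as a range starting near zero.

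The calculations omit centre. At the planned rates and 191 per arm there would be about 191 × 0.35 + 191 × 0.20 ≈ 105 events, spread over centres whose number is not used here. How centre terms and four covariates behave together is untested, so the handling of small centres must be prespecified.

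A reader might infer three stronger things that the document does not support:

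- **That the primary result would be biased or the trial underpowered.** The plan's figure of 181 per arm reproduces, and stratum adjustment is sound.
- **That the interval for the absolute risk reduction will be too wide because it ignores stratification.** This presumes a crude difference in proportions, which the protocol never states.
- **That the timing of data collection rules these covariates out.** The confidentiality section lists the other collected data after randomisation, while Table 1 places them at enrollment. Their values are fixed by birth and come from clinical records, so the time of entry changes nothing.

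**Conclusion.** The point holds as one of efficiency. The protocol fixes a valid but somewhat inefficient primary adjustment set, while recording baseline variables that could sharpen the estimate without further data collection. The likely benefit is modest: about 0.5 to 10% lower variance, an interval up to about 5% narrower, and 0 to 3 points of power. The lower end applies if the variables are weakly prognostic, in which case almost nothing is gained. These figures depend on assumed covariate effects, assumed age distributions and the omission of centre. The case for changing rests on the low cost, not on a defect in the planned test.

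**What to change.** Before any by-arm outcome is analysed:

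- **Section {20a}, covariates.** Adjust the primary model for the stratification factors plus continuous gestational age, sex, birth-weight z score and complete antenatal steroid course.
- **Section {20a}, estimation.** Estimate the RR from a logistic model standardised over all infants, or from a modified Poisson model with robust variance, instead of adding continuous terms to the log-binomial model. Take the absolute risk reduction and number needed to treat from the same adjusted analysis. Prespecify how small centres are handled.
- **Section {20a}, sensitivity analysis.** Keep the stratification-only log-binomial RR.
- **Section {20c}.** As written, its ban on imputation would drop any infant with a missing covariate from the adjusted model. Restrict the ban to outcomes, and allow a rare missing baseline covariate to be filled by a simple rule that ignores treatment arm, so that no infant leaves the intention-to-treat analysis.

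Cost: no new data and no more infants, but more than a wording change. The trial is recruiting, and section {25} requires important modifications to be approved by all the ethics committees and reported. There is slightly more programming, and if standardisation is used the primary RR becomes a standardised estimate and not a single model coefficient.
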